### Adoption of The CONNECT program

Adoption is defined as the intention, initial decision, or action to try or employ an innovation or evidence-based practice [63]. Data will be collected through a post-program survey that includes Likert-scale and open-ended questions (with items developed based on [63]. In addition, a weekly facilitator check-in questionnaire will track dropout, attendance, and participant-reported reasons for not attending or discontinuing.

### Appropriateness of The CONNECT program

Appropriateness is the perceived fit, relevance, or compatibility of the innovation or evidence-based practice for a given setting, provider, or consumer, and/or the perceived fit of the innovation to address a particular issue or problem [63]. Data will be collected through a post-program survey that includes Likert-scale and open-ended questions (with items developed based on [63], an exit interview, the Intervention Content evaluation (adapted from [64]), and the Intervention Delivery Type evaluation (also adapted from [64]). In addition, a weekly facilitator check-in questionnaire will track dropout, attendance, and participant-reported reasons for not attending or discontinuing.

### Feasibility of The CONNECT program

Feasibility is defined as the extent to which an innovation can be successfully used or carried out within a given agency or setting [63]. Data will be collected through a post-program survey that includes Likert-scale and open-ended questions (with items developed based on [63], an exit interview, the Intervention Content evaluation (adapted from [64]), and the Intervention Delivery Type evaluation (also adapted from [64]. In addition, a weekly facilitator check-in questionnaire will track dropout, attendance, and participant-reported reasons for not attending or discontinuing.

### Implementation Costs of The CONNECT program

Implementation costs are defined as the cost impact of an implementation effort [63]. Data will be collected through a post-program survey that includes Likert-scale and open-ended questions (with items developed based on [63]).

### Penetration of The CONNECT program

Penetration refers to the integration of an innovation within a service setting and its reach among intended users. At the recipient level, it is defined as the number of eligible individuals who use a service, divided by the total eligible population. At the setting level, it is the number of providers delivering the service, divided by the total number trained or expected to deliver it [63]. Data will be collected through a post-program survey that includes Likert-scale and open-ended questions (with items developed based on [63]).

### Sustainability of The CONNECT program

Sustainability is defined as the extent to which a newly implemented treatment is maintained or institutionalized within a service setting’s ongoing, stable operations [63]. Data will be collected through a post-program survey that includes Likert-scale and open-ended questions (with items developed based on [63]). In addition, a weekly facilitator check-in questionnaire will track dropout, attendance, and participant-reported reasons for not attending or discontinuing.

A detailed overview of the assessment schedule by timepoint and study week is provided in Table 1.

**Table 1 pone.0336031.t001:** Schedule for assessment administration.

	TRIAL PERIOD						
	Enrollment		Post-randomization				6-month follow-up
Timepoint	*−1*	0	*T1*	*T2*	*T3*	*T4*	*T5*
Timing	*Week *(−4)	Week 0	*Week 1 -Week 6*	*Week 6*	*Week 7 -Week 12*	*Week 12*	*Week 30–36*
Sociodemographics		X^1,2^					
Psychological flexibility (Acceptance and Action Scale; [47]) Acceptance and Commitment Scale		X^1,2^		X^1,2^		X^2^	X^1,2^
DeJong Gierveld Loneliness Scale [53]		X^1,2^		X^1,2^		X^2^	X^1,2^
Social Isolation (PROMIS Social Isolation 8a; [55]		X^1,2^		X^1,2^		X^2^	X^1,2^
Emotional Support (PROMIS Emotional Support; [55])		X^1,2^		X^1,2^		X^2^	X^1,2^
Anxiety (PROMIS Anxiety Short Form 4a; [56])		X^1,2^		X^1,2^		X^2^	X^1,2^
Depression (PROMIS Depression Short Form 4a; [56])		X^1,2^		X^1,2^		X^2^	X^1,2^
Mental Health Literacy (Brief Mental Health Literacy Scale; [61]		X^1,2^		X^1,2^		X^2^	X^1,2^
Group Session Scale [65]			X³		X³		
Intervention Delivery Type (Adapted from [64]				X^1^		X^2^	
Intervention Content (Adapted from [64]				X^1^		X^2^	
Individual Qualitative Exit-Interview				X^1^		X^2^	
Implementation Survey (Likert-scale and open-ended items, per [63].)				X^1^		X^2^	
Weekly Facilitator Check-in Questionnaire			X³		X³		

X¹ - Participants who received The CONNECT Program first, X² - Participants who received The CONNECT Program second (after waitlist), X³ - Weekly administration during the CONNECT Program sessions only; not completed during control condition.

Risks of the trial are minimal but may include psychological and emotional discomfort when discussing topics like social isolation, loneliness or mental health. Facilitators monitor participants during sessions and respond to distress following a structured safety protocol. A mental health resource list is provided to all participants, and those in the control condition continue to receive service as usual.

The trial has a target recruitment of 128 participants, with 64 in each delivery group (videoconference and telephone), based on a power calculation with Cohen effect of 0.5 alpha = 0.05 and power 80%. The effect size of 0.5 is based on our pilot data and is consistent with other similar intervention studies in older adults (e.g., [66]).

Participants will be recruited through the four partnering community organizations, with local community partners overseeing outreach. Each site will run two groups per delivery mode (videoconference and phone), with approximately 32 participants recruited per site. To support both recruitment and retention, participants will receive a $25 honorarium (e-gift card or mailed) after completing each of the three assessment points baseline, post-intervention, and follow-up – for a total of $75. An additional $25 honorarium will be provided to participants who are selected at random for qualitative interviews after participating in The CONNECT Program (n = 40; 10 per site).

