## Materials and methods

### Patient and public involvement, trial design

Before launching the trial, a few pre-implementation studies were conducted together with the partner community organisations across three provinces (British Columbia, Manitoba, Saskatchewan) and adult participants aged 55 + . We completed one virtual focus group per province with staff from each of the partner sites to gather input on how to adapt The CONNECT Program for different provinces [41–43]. This included feedback on revising the materials to reflect local needs, choosing the best delivery format (phone or videoconferencing), and designing a training and supervision process for community-based facilitators. We also held virtual focus groups and interviews with adults aged 55+ to learn about their mental health support needs, views on The CONNECT Program and implementation preferences [44].

This study uses a randomized crossover trial design, embedded within a type 1 hybrid implementation-effectiveness framework [45]. Participants are randomly assigned in a 1:1 ratio to begin either with The CONNECT Program or with the community-based programming. After completing the first condition, they will cross over to the other condition. Two sites will begin with videoconference mode and then switch to telephone mode, while the other two will follow the opposite sequence. In this RCT the effectiveness and implementation outcomes follow a superiority framework. Recruitment is ongoing in four Canadian provinces, with site-specific recruitment periods. The recruitment started on 8 September 2025, and is ongoing, with recruitment date for both primary and secondary end point collection expected to be collected by 30 September 2026.

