**Fig 1 pone.0336031.g001:**
[figure not shown]
Schedule of enrollment, interventions, and assessments. X¹ - Participants who received The CONNECT Program first. X² - Participants who received The CONNECT Program second (after waitlist). Each participant is randomized to one of two treatment sequences – either starting with The CONNECT Program followed by community-based programming, or vice versa. A crossover occurs at the transition between week 6 and week 7. The 6-month follow-up will be conducted 24 weeks after each participant completes The CONNECT Program, which may fall between weeks 30 and 36 depending on their assigned treatment sequence.

Prior to delivering the program, all facilitators complete a structured training program led by the research team. Training includes an introduction to the theoretical foundations of the program, facilitation skills for telehealth delivery, safety and crisis response planning, and an in-depth review of The CONNECT Program content and structure. Facilitators may also seek clinical supervision or consultation through weekly national meetings with the study team and other facilitators across sites during program delivery to support implementation challenges. All facilitators will take part in the same training and receive supervision support throughout the program to make sure its delivery is consistent and high-quality across locations.

Participation in the trial is voluntary; participants can withdraw at any time with no reason. If a participant experiences significant emotional distress or expresses suicidal thoughts, the facilitator will follow a safety protocol, which may include pausing the participant’s involvement and referring them to appropriate mental health support. Facilitators track weekly attendance and maintain regular contact with participants. Homework completion is encouraged and followed up on during sessions. Participants may continue any existing treatment, including medication or therapy to simulate real-world conditions, however, they are asked to avoid joining new mental health support groups during the trial to reduce interference with outcome interpretation, though adherence to this cannot be enforced. The effectiveness of The CONNECT Program will be examined through a set of primary and secondary outcomes, described below; implementation of the program will be assessed through other pre-specified outcome.

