Analysis of the primary and secondary outcomes will be conducted using linear mixed-effects models to account for repeated measures and the crossover design. Changes in psychological flexibility, loneliness, social isolation, emotional support, anxiety, depression, and mental health literacy will be compared between The CONNECT Program and control conditions using repeated measures analyses, adjusting for delivery sequence and baseline values. For descriptive comparisons, both paired t-tests and repeated measures ANOVA may be used. Adverse events and participant distress will be recorded; however, harms will not be systematically evaluated. All analyses will be performed on a per-protocol basis, including only participants who complete both stages. Sensitivity analyses may include a larger sample, if applicable. Missing data will be examined for patterns; if data are missing at random, linear mixed models will be used. For key outcomes with high levels of missingness, multiple imputation or pattern-mixture models will be considered. Subgroup analyses by delivery mode and location will be conducted if sample sizes are sufficient to support interpretation.

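### Table 1 takes no week-12 outcomes in CONNECT-first participants, so the planned crossover effect is not estimable with sequence and period both in the model; only the week-6 randomised comparison is intact

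*Protocol article*

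**What the plan says.** The trial design section assigns participants 1:1 to one of two orders and adds that "After completing the first condition, they will cross over to the other condition". The Fig 1 legend places the switch: "A crossover occurs at the transition between week 6 and week 7". Period 1 is therefore weeks 1 to 6 and period 2 is weeks 7 to 12.

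The analysis paragraph, under Assignment of interventions, plans "linear mixed-effects models to account for repeated measures and the crossover design". It contrasts CONNECT with control adjusting for delivery sequence and baseline, allows paired t-tests for descriptive comparisons, and limits all analyses to people who finish both stages.

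Table 1 marks the AAQ-II and the six secondary scales for both sequences at week 0, week 6 and T5. At week 12 it marks only X², which the key defines as "Participants who received The CONNECT Program second (after waitlist"; X¹ stands for CONNECT first.

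On T5, the Fig 1 legend says "The 6-month follow-up will be conducted 24 weeks after each participant completes The CONNECT Program". The recruitment text after Table 1 pays $25 "after completing each of the three assessment points baseline, post-intervention, and follow-up", $75 in total.

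**The concern.** A two-period crossover earns its precision, and its protection against time trends, by measuring each person under both conditions in two opposite orders. Here one order has no outcome at the end of its control period. Control-first participants do have a control score (week 6) and a CONNECT score (week 12), but always in that order. At T5 everyone has had CONNECT, so there is no control there either.

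This affects the primary outcome, every secondary effectiveness outcome and the trial's stated design. Recruitment began on 8 September 2025 and is described as ongoing. A CONNECT-first participant who passes week 12 unmeasured cannot be measured later.

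**Working it through.** **1. What is observed.** Table 1 set against the two sequences:

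| Sequence | Week 6 | Week 12 |
|---|---|---|
| CONNECT first (A) | CONNECT, measured | control, not measured |
| Control first (B) | control, measured | CONNECT, measured |

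T5 cannot fill the empty cell. For sequence A it falls at week 6 + 24 = 30, which is 30 − 12 = 18 weeks after the control period ended. For sequence B it falls at 12 + 24 = 36.

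**2. Estimability.** Write a cell mean as μ + s (if sequence A) + p (if week 12) + t (if under CONNECT). The observed cells are:
- A6 = μ + s + t
- B6 = μ
- B12 = μ + p + t

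The missing cell is A12 = μ + s + p. Three equations for four unknowns give rank 3. The data yield only A6 − B6 = s + t and B12 − B6 = p + t, so t is not separately estimable. With A12 added the rank is 4 and t is estimable.

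**3. What happens when a term is left out.**
- Period kept, sequence dropped: t = A6 − B6, with weights +1, −1 and 0 on A6, B6 and B12. This is the week-6 between-group difference. Week 12 only informs the period effect.
- Sequence kept, period dropped, or a paired t-test in sequence B: t = B12 − B6. Any six-week trend enters one-for-one.
- Both dropped: the estimate is w·B12 + (1 − w)·A6 − B6. With equal variances and within-person correlation ρ, minimising w² + (1 − w)² + 1 − 2wρ gives w = (1 + ρ)/2. For ρ = 0.3, 0.5 and 0.7 (assumed; the article gives no correlation), 65%, 75% and 85% of a trend enters.
- Week 0 modelled as a repeated outcome: sequence becomes identifiable, but t = (A6 − A0) − (B6 − B0), which is still the week-6 between-group contrast.

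**4. The plan's own figure.** Inputs are d = 0.5, alpha 0.05 and power 80%; two-sided testing is assumed because sidedness is not stated. The normal formula n = 2(1.960 + 0.842)²/0.5² = 62.8 gives 63 per group. The two-sample t-test gives 63.8, so 64 per group and 128 in total, as stated. A paired calculation would need only (1.960 + 0.842)²/0.5² = 31.4, about 32 pairs. The stated size is thus that of two independent groups. The article's 64 + 64 is by delivery mode; 64 per sequence is my assumption from 1:1 allocation of 128.

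**5. Precision, 64 per sequence, SD units.**
- Week-6 comparison: variance 2/64 = 0.03125, SE 0.177. Power at d = 0.5 is Φ(0.5/0.177 − 1.96) = 80.7%, or 80.1% with the t distribution.
- Full crossover: variance (1 − ρ)/64, so SE 0.105, 0.088 and 0.068 for ρ = 0.3, 0.5 and 0.7, and power above 99%.
- Variance ratio 2/(1 − ρ): 2.9, 4.0 and 6.7.

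These figures ignore carryover, dropout and clustering by group.

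**6. Payments.** Outcome assessments number three in CONNECT-first (weeks 0, 6, T5) and four in control-first (weeks 0, 6, 12, T5). Paid points: three.

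**The case against.** The strongest defence is that the article condenses a fuller plan, that the mark could be a slip, and that the trial can still answer its question. Some of this stands.

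A fuller plan may well specify a period term, which the article neither includes nor excludes, and delivery sequence might even refer to the video/telephone order. A reader might infer that every pooled estimate is biased by the full time trend. The documents do not support that: with period included and sequence dropped, the estimate is the unbiased week-6 contrast. But no analysis plan can recover a score that is never scheduled. A slip is also unlikely. The mark repeats in all seven rows, the three paid points match the CONNECT-first schedule, and the footnote's reference to a waitlist fits a delayed-start layout, although the comparator is active programming.

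A reader might also infer that the trial cannot compare CONNECT with control at all. It can, at week 6, where both randomised groups are measured.

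Simply filling the empty cell is not a complete remedy. The Discussion concedes that there is no formal washout and that psychological changes may persist. A week-12 score in CONNECT-first participants may therefore carry some CONNECT effect and pull a crossover estimate toward no difference.

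Finally, a reader might infer that week 6 is unpaid in control-first participants and that differential missingness follows. The article does not say so. The word post-intervention may mean after CONNECT or after the first condition. Only the mismatch of three payments and four assessments is fact.

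**Conclusion.** The schedule and the planned crossover analysis contradict each other. Under Table 1 no CONNECT-first participant supplies a within-person CONNECT-versus-control pair. At most 64 of 128 participants do, and in those 64 treatment and period cannot be separated. The crossover effect is not estimable with sequence and period both in the model.

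What is lost is the within-person estimate and its precision (a variance 2.9 to 6.7 times larger for assumed correlations of 0.3 to 0.7), not the ability to test CONNECT. The week-6 comparison keeps about 80% power at d = 0.5. That figure assumes two-sided testing, 64 analysed per sequence and no clustering. It would be lower after dropout, and restricting week 6 to people who later finish stage two would select on events after that comparison.

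The point must be fixed, because it concerns the primary outcome and the missing scores cannot be collected afterwards.

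**What to change.** Reconcile Table 1 with the analysis paragraph in one of two ways.

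1. **Week-6 parallel comparison.** Define the primary analysis as the baseline-adjusted week-6 difference between sequences, describe the trial as parallel-group with delayed CONNECT, and report week 12 and T5 as within-group change only. This costs wording, plus the crossover label and its within-person precision.
2. **Complete the crossover.** Mark week 12 for both sequences for the AAQ-II and the secondary scales, and include period in the model. Keep week 6 as the primary or key sensitivity estimate because of possible carryover. This costs up to 64 more short assessments, some given verbally by a research assistant, and 64 × $25 = $1,600 if they are paid.

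These are alternatives. Once week 12 is measured in both sequences, it would no longer be right to report it as within-group change only.

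Separately, under either option, state which assessments carry the honorarium and pay week 6 equally in both sequences. Paying the fourth control-first assessment would add up to 64 × $25 = $1,600.

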### Assignment of interventions

Randomization will be conducted by a non-affiliated researcher at the Centre for Healthcare Innovation (CHI) using a secure computerized tool. We are using restricted randomization to keep group sizes balanced within each site. Details about blocking and sequence structure are recorded separately and will not be shared with staff involved in recruitment or group assignment prior to randomization. Each participant will be assigned a unique ID and randomized into one of two sequences: The CONNECT Program first or Community Programming as Usual first. Participants will be randomized prior to enrollment. The research coordinator will be aware of group assignment after randomization to manage scheduling and follow-up; however, outcome assessor and outcome analysts will remain blinded and only work with de-identified data. Group assignment will not be disclosed to the outcome assessor or analysts, and all outcome data will be labeled using participant ID codes without identifying group allocation. Due to the nature of the behavioral interventions, neither participants nor facilitators will be blinded. We do not expect unblinding to be necessary for the assessor or analysts.

If participants are unable to self-administer via a secure link then measures will be administered verbally by a trained research assistant via telephone or university-managed Zoom and responses input on the behalf of a participant. To support data quality, assessors will be trained in standardized procedures, and data will be entered directly into REDCap, which includes built-in range checks. Duplicate entries and inconsistencies will be identified during routine data cleaning. Each participant will be assigned a unique ID number to ensure confidentiality. All data will be stored on secure University of Manitoba (UM) REDCap servers and transferred to a password-protected UM OneDrive folder in accordance with the data transfer agreement, only the research team will have access to identified data.

To promote retention, participants will receive reminders for each assessment and session, along with technical assistance where needed. In cases where participants discontinue or miss sessions, they will still be invited to complete follow-up assessments, including key outcome measures where possible.

Analysis of the primary and secondary outcomes will be conducted using linear mixed-effects models to account for repeated measures and the crossover design. Changes in psychological flexibility, loneliness, social isolation, emotional support, anxiety, depression, and mental health literacy will be compared between The CONNECT Program and control conditions using repeated measures analyses, adjusting for delivery sequence and baseline values. For descriptive comparisons, both paired t-tests and repeated measures ANOVA may be used. Adverse events and participant distress will be recorded; however, harms will not be systematically evaluated. All analyses will be performed on a per-protocol basis, including only participants who complete both stages. Sensitivity analyses may include a larger sample, if applicable. Missing data will be examined for patterns; if data are missing at random, linear mixed models will be used. For key outcomes with high levels of missingness, multiple imputation or pattern-mixture models will be considered. Subgroup analyses by delivery mode and location will be conducted if sample sizes are sufficient to support interpretation.

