### Monitoring

A formal Data Monitoring Committee (DMC) was not impaneled for this trial because The CONNECT Program is a low-risk, non-pharmacological behavioral intervention. In accordance with ethical conduct, the principal investigator and study team will provide monitoring of this study. Interim analyses or stopping guidelines are not planned with this short trial and small number of enrolled participants, who are exposed to little risk. Any negative experiences or unexpected issues (e.g., distress among participants) will be managed by the study team. The study coordinator and principal investigator will oversee the daily administration of the program – recruitment, delivery of interventions, attendance, and data collection. The study team will meet on a regular basis to review the progress of the trial and consider any new issues, which have arisen.

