### Ethics

This study has received ethical approval from the University of Manitoba Research Ethics Board (REB #HE2024−0150). Any protocol amendments will be submitted for further review and approval. Any significant protocol modifications (e.g., changes in eligibility criteria, outcomes, or procedures) will be communicated to the REB, research team members, community partners, and participants as appropriate. We will provide two options for consenting, with a preference for the first option where feasible. The first option is to electronically sign the consent form in REDCap. If a participant does not have access to a computer/internet, we will offer the alternative of providing verbal consent for participation in the study. Verbal consent will be obtained via telephone and documented in REDCap. The researcher (research coordinator or research assistant) conducting the consenting process over the phone will note the participant’s full name, the date the consent was given, and their own name, indicating who received the consent. Subsequently, we will mail two copies of the consent form to the participant’s residence for their records. Identifiable information will be kept separate from survey responses and stored on secure, password-protected servers. Data will be retained according to institutional data management policies.

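### The article randomises participants before enrolment and tells a coordinator who may take consent the result, while Table 1 implies the reverse order; as worded, allocation is not concealed at entry

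*Protocol article*

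**What the plan says.** **Order of events.** The protocol article, under Assignment of interventions, says: "Participants will be randomized prior to enrollment." Table 1 places week −4 and week 0 under an enrolment heading, including every baseline questionnaire. The columns from week 1 to week 12 come under a post-randomization heading.

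**Who knows the allocation.** The same section says: "The research coordinator will be aware of group assignment after randomization to manage scheduling and follow-up." Details of blocking and sequence structure "will not be shared with staff involved in recruitment or group assignment prior to randomization".

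**Who takes consent.** The Ethics section describes two routes. The preferred one is electronic: "The first option is to electronically sign the consent form in REDCap." The alternative is verbal consent by telephone, and the person taking it is described as "The researcher (research coordinator or research assistant) conducting the consenting process over the phone". Under Monitoring, "The study coordinator and principal investigator will oversee the daily administration of the program – recruitment, delivery of interventions, attendance, and data collection."

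**Blinding.** Under Assignment of interventions, "neither participants nor facilitators will be blinded", whereas "outcome assessor and outcome analysts will remain blinded and only work with de-identified data". All effectiveness outcomes are self-reported, and the analysis paragraph adjusts for baseline values.

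**The concern.** Concealment means that nobody who can influence whether a person joins, and not the person either, knows the coming allocation until entry is irrevocable. On the article's wording, allocation exists before enrolment, and a role that may conduct consent knows it.

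Two things are at stake.

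- **Selection at entry.** The two sequences need not be equally attractive. The Fig 1 legend and the Table 1 footnote describe those who receive CONNECT second as having waited for it. If people decline, or are encouraged differently, according to sequence, the groups that enter are no longer those that randomisation formed. Baseline adjustment removes only the part of that difference which the measured baseline captures. The main analysis set is limited to participants who complete both stages, so those lost after allocation are not brought back.
- **Baseline measurement.** The Acceptance and Action Questionnaire-II is a self-report. If a participant knows the sequence when answering at week 0, the covariate is in effect measured after randomisation, and adjusting for it no longer has its usual justification.

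**Working it through.** The point is one of procedure, so the check is to set the statements side by side.

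1. **Randomisation against enrolment.** Assignment of interventions puts randomisation first. Table 1 puts enrolment and the week 0 questionnaires before the post-randomization columns. With 'enrollment' used in the same sense, both cannot be true. No other section states that consent and the week 0 assessment come before randomisation or before release of the result.

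2. **Allocation known against consent taken.** The research coordinator knows the assignment from randomisation. The Ethics section names the research coordinator as one of two roles that may take telephone consent. With the order in step 1 as worded, a consent-taker can know the sequence beforehand. The Monitoring section adds oversight of recruitment by a study coordinator. I take this to be the same role, but the point does not depend on it.

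3. **Reach of the safeguard.** Withholding the blocking details is tied to the time before randomisation. On this wording that time ends before enrolment starts. Hiding the block structure makes future allocations hard to guess. It does nothing once the individual's own allocation has been disclosed.

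4. **Baseline.** Table 1 places the week 0 measures inside the enrolment period. If enrolment follows randomisation, so do those measures. The article does not say when participants are told their sequence.

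5. **Which comparison is exposed.** In Table 1 the outcome questionnaires are given to both sequences at weeks 0 and 6, but at week 12 only to those who receive CONNECT second. The CONNECT-first sequence therefore has no measure at the end of its control period. The only time at which both conditions are measured concurrently at the end of a period is week 6, and that comparison is between sequences, which is what concealment protects.

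**Size.** The article gives no refusal rates and no characteristics of refusers, so no bias can be computed. The following uses assumed inputs only, to show how far the answer depends on them. If a proportion *r* of a sequence refuses after learning its allocation, and refusers differ from the mean of all randomised by *s* SD, the mean of those who remain shifts by *r·s*/(1 − *r*). The imbalance between sequences is the difference of two such shifts.

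| Assumed refusal, two sequences | Assumed *s* | Imbalance (SD) |
|---|---|---|
| equal | same in both | 0 |
| 5% and 15% | 0.3 | 0.15×0.3/0.85 − 0.05×0.3/0.95 = 0.04 |
| 5% and 15% | 0.5 | 0.15×0.5/0.85 − 0.05×0.5/0.95 = 0.06 |
| 10% and 30% | 0.3 | 0.30×0.3/0.70 − 0.10×0.3/0.90 = 0.10 |
| 10% and 30% | 0.5 | 0.30×0.5/0.70 − 0.10×0.5/0.90 = 0.16 |

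These are imbalances before any baseline adjustment, not biases in the planned estimate.

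**The case against.** The strongest reply is that the defect hangs on one undefined word. 'Enrollment' may loosely mean joining a programme group. Table 1 fits the conventional order, and withholding sequence details from recruitment staff until randomisation also fits recruitment coming first. This stands as a reason for caution. A reader might infer that concealment has actually failed, and the article does not establish that. It does not remove the contradiction, because the sentence is written as a rule and nothing else in the article corrects it.

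Second, a researcher outside the study team carries out the randomisation by computer. That protects generation of the sequence, but not entry, if the result is released before consent.

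Third, the coordinator is named as consent-taker only for the telephone route, which is the fallback, and a research assistant may do it instead. This stands: the article does not support the reading that the coordinator takes everyone's consent.

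Fourth, that participants know their sequence when they complete the week 0 measures is an inference. Being unblinded during treatment says nothing about when they were told. This also stands, so contaminated baselines are a possibility that the wording leaves open and not a stated fact. Blinding of assessors and analysts would not prevent it, because the scores are self-reported.

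Fifth, each participant is due to receive both conditions, which weakens the motive to refuse and makes within-person contrasts less sensitive to imbalance. This holds only in part, given the missing week 12 measure in the CONNECT-first sequence and, as the Discussion acknowledges, no formal washout.

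Finally, a reader might set an assumed imbalance against the planned effect of 0.5 and call the ratio the bias. The documents do not support that: the inputs are invented, and the planned model adjusts for baseline.

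**Conclusion.** The point holds as a contradiction within the article, with a serious consequence if the wrong side of it is followed. Assignment of interventions, Table 1 and Ethics cannot all be followed as they stand. Under the first, allocation is not concealed from a role that may take consent, and the baseline covariate could be collected after the sequence is known.

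Confidence in the contradiction is high. Whether bias has arisen is unknown. It depends on three things that the article does not settle: what 'enrollment' means, when the allocation is released to the coordinator and to participants, and how often consent goes through the coordinator. The size cannot be estimated from the document. The correction should still be made now, because recruitment began on 8 September 2025 and is continuing, and selection at entry cannot be fully repaired in the analysis.

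**What to change.** - Reconcile Assignment of interventions, Table 1 and Ethics by replacing the sentence on timing with: *Participants are randomised only after eligibility is confirmed, consent is documented in REDCap and the T0 assessment is complete; the allocation is released to the coordinator only after that.* Here T0 is the week 0 timepoint of Table 1. A check in REDCap that blocks release until these steps are complete would enforce the order.
- Report everyone randomised, by sequence, in the flow diagram, including any who did not go on to enrol.
- For participants already recruited, record whether consent and the week 0 assessment preceded release of the allocation, and report this by sequence. Excluding those for whom they did not should not be a required analysis. If the current sentence was applied literally, exclusion could remove everyone recruited so far. If timing differed by sequence, exclusion could itself introduce selection.

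The cost is procedural. Groups of 6 to 8 must be filled from people who have already consented and completed baseline, which may slightly delay a group start.
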